#### Participant timeline

Recruitment will take place from April 2014 to December 2015. Each participant will be enrolled in the study for approximately 25 months in total (1-month RCT – diagnosis and treatment, followed by a 24-month observational period). The timeline with details of the data collection schedule are summarized in Fig. 1.

**Fig. 1 Fig1:**
[figure not shown]
Timeline of the study procedures

#### Sample size

The sample size calculation was based on the occurrence of the primary outcome: number of dental surfaces of primary molars with operative needs during the follow-ups and the incidence data. Considering operative needs, we observed a mean of 17.6 surfaces with new caries lesions after 2 years [31], approximately 10 % restoration failure of occlusal or occluso-proximal restorations in 2 years [32], 0.08 extracted teeth in 2 years, with 0.2 surfaces [33] and 0.3 pain episodes in 2 years, with one surface [33].

Therefore, a mean of 19 surfaces with treatment need in the visual inspection alone group is expected. A difference of five surfaces with treatment need in the visual plus radiographic method group was considered as a minimally clinically important difference. The standard deviation values expected for visual and visual plus radiographic groups were 15 and 10, respectively. Therefore, using a two-tailed test and considering a significance level of 5 % and 80 % power, the minimum sample size of children calculated was 103 per group. Anticipating an attrition rate of 80 %, the final minimum sample size was 250 children for the entire study.

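### An 80 % attrition rate cannot lead from 103 children per group to a total of 250, so the assumed rate must be restated

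*Protocol article*

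**What the plan says.** The Sample size section plans a comparison of mean numbers of surfaces needing operative treatment. The expected mean under visual inspection alone is 19, the smallest important difference is 5, and the standard deviations are 15 (visual) and 10 (visual plus radiographic). The test is two-tailed at 5 % with 80 % power. From this, "the minimum sample size of children calculated was 103 per group".

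The next sentence makes the allowance for loss. It opens "Anticipating an attrition rate of 80" per cent and ends "the final minimum sample size was 250 children for the entire study".

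The abstract repeats the total of 250. No other section of the article gives an attrition or retention rate. Follow-up lasts 24 months, and the Trial status section reports 225 children already included when the article was submitted.

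**The concern.** A loss of 80 % is far too large to be covered by raising 206 to 250. Either the rate is misprinted or the total is wrong, and a reader cannot tell which from the text.

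The obvious repair, replacing 80 by 20, does not fully reconcile the figures either. A 20 % loss from 250 leaves fewer than 103 per group.

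The anticipated rate is the yardstick for judging actual loss over two years of follow-up. As printed, losing most of the children would count as expected. The power statement also matters for interpretation. The authors expect radiographs to add little and hope to refute the recommendation for routine bitewings, so a null result will be read against the stated power and the loss the design was said to tolerate.

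**Working it through.** **Inputs** (all from the Sample size section): difference 5; standard deviations 15 and 10; two-sided 5 %, so z = 1.96; power 80 %, so z = 0.8416; equal arms. The mean of 19 does not enter the formula.

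**Step 1. Reproduce the stated 103.**
n per group = (1.96 + 0.8416)² × (15² + 10²) / 5² = (2.8016)² × 325 / 25 = 102.04, rounded up to 103.
The stated figure is correct. Two groups need 206 evaluable children. Power at 103 per group is 80.4 % by the normal approximation and 79.9 to 80.0 % by the noncentral t.

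**Step 2. Apply the stated 80 % attrition.**
- Dividing by the retained fraction: 206 / (1 − 0.80) = 1030.
- Multiplying by one plus the rate, a common shortcut that inflates too little: 206 × 1.80 = 370.8, so 371.
- Working back from 250: 250 × 0.20 = 50, or 25 per arm. Power there is about 27 % (noncentral t) or 28 % (normal).

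Neither rule gives 250.

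**Step 3. Assume 20 % attrition (80 % retention).** This rate is an assumption and is not in the article.
- Needed: 206 / 0.80 = 257.5, so 258 (129 per group).
- Starting from the unrounded 102.04 per group: 2 × 102.04 / 0.80 = 255.1, still above 250.
- Left from 250: 250 × 0.80 = 200, or 100 per arm, which is 3 short per arm and 6 short in all.
- Power at 100 per arm: standard error = √(325/100) = 1.803; 5/1.803 − 1.96 = 0.81; power 79.2 % (normal). The noncentral t gives 78.8 %.

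**Step 4. Find the loss that 250 can absorb.**
1 − 206/250 = 0.176. The total keeps 103 per group as long as attrition is at most 17.6 %, which is 44 children in all or 22 per arm if losses are equal.

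| Attrition | Total needed to keep 206 | Left per arm from 250 | Power with 250 |
|---|---|---|---|
| 80 % (as printed) | 1030 | 25 | about 27 % (t) |
| 20 % (assumed) | 258 | 100 | 78.8 % (t), 79.2 % (normal) |
| 17.6 % (break-even) | 250 | 103 | 79.9 to 80.0 % (t), 80.4 % (normal) |

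**The case against.** The strongest reply is that this is a slip in reporting and not a flaw in the design. Nobody who raised 206 to only 250 was expecting to lose four children in five. The figure of 25 per arm therefore shows that the sentence is wrong, but it does not measure a risk to the trial. That stands.

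A reader might go further and infer that the trial is underpowered because 250 fails to deliver 80 % power on the intended reading. The article does not support this. It never states 20 %, and 250 is sufficient for any loss up to 17.6 %. Even at 20 % the deficit is about one percentage point of power, which is small beside the uncertainty in round planning values such as standard deviations of 15 and 10.

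A reader might also infer that 250 came from the shortcut 206 × 1.2 = 247.2, rounded up. The number is close, but the article gives no inflation formula, and 250 could equally be a rounded total for a lower rate.

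The objection does not remove the contradiction. Nothing else in the article gives the rate, and putting 20 in place of 80 still does not yield 250.

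**Conclusion.** The sentence is wrong as written. That follows from the article's own numbers and needs no assumption beyond equal arms: 80 % attrition would call for 1030 children, not 250.

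The second part is conditional. If the sponsor confirms 20 % attrition, 250 is 8 below the 258 required and power is about 79 %. That is a small shortfall and should not be presented as a material loss of power. If the assumed rate was 17.6 % or lower, 250 is adequate and only the printed rate is at fault.

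The point deserves correction because the sample size rests on this figure, but it gives no reason to change the design.

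**What to change.** The sponsor should state the attrition rate actually assumed; it should not be filled in as 20 % without confirmation. Keep 250, and add one of two statements:

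- 250 children preserve 103 per group, and so 80 % power, for attrition up to 17.6 %; or
- if 20 % is confirmed, 250 children leave 100 per group and power of about 79 %.

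The cost is one corrected sentence and, in the second case, a stated power about one point lower. No further enrolment and no change to the design or analysis is needed.

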#### Recruitment

Recruitment is based in our School of Dentistry, which refers children who seek dental care.

### Assignment of interventions

#### Allocation: sequence generation

The participants will be selected from a pool of enrollment forms of children who looked for dental treatment in our school, using a sequence of random numbers generated by software. The randomization procedure will be done per blocks of the same size and stratified by age and caries experience groups.

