#### Interventions

An initial clinical examination will be performed to evaluate the teeth present in the mouth, as well as the caries experience using the World Health Organization criteria [14]. The children will be classified in subgroups according to age (3 and 4 years old or 5 and 6 years old) and according to the caries experience (children with decayed-missing-filled-surfaces (dmf-s) less than or equal to 3 or children with dmf-s greater than 3).

If the child is eligible to participate in the study, bitewing radiographs will be taken from each side, including the upper and lower primary molars (two bilateral radiographs for each child), as recommended by different clinical guidelines throughout the world [5–7]. Complementary periapical radiographs also will be taken when necessary. Radiographs will be processed using the time/temperature method, in which the film stays in the revealing solution (Eastman Kodak, Rochester, NY, USA) for 2 min at a temperature of approximately 27 °C [15], followed by a fixation time of 10 min in fixing solution (Eastman Kodak, Rochester, NY, USA), and then by washing in water for 20 min [15]. The revealing and fixing solutions will always be new, replaced at the beginning of each period of clinical appointments, guaranteeing the quality of processing.

In addition, a questionnaire to evaluate the impact of oral health on the quality of life of the children at baseline will be applied for the parents. The instrument used will be the Brazilian version of the Early Childhood Oral Health Impact Scale (ECOHIS) [16, 17]. Then, the participant will be randomly allocated in one of the two groups.

The groups will be defined according to the diagnostic strategy used for reaching the treatment decision related to dental caries in primary molars proposed for each child. The two groups are as follows:Visual inspection alone: The treatment decision plan will be based only on a visual inspection. The examiners will not receive the bitewings of these children to elaborate the treatment plan. They will only access periapical radiographs when necessary (to decide between endodontics or tooth extraction, for example); those radiographs will be available after the decision regarding the process for the other teeth has been rendered.Visual inspection plus radiographic: The treatment plan will be based on the visual inspection complemented by radiographic examination. The access to periapical radiographs is also permitted in this case.

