#### Allocation concealment mechanism

We will use sealed, sequentially numbered, opaque envelopes, separated by each stratum. The randomization will be done after the inclusion of the child and after the radiographs. The group will be revealed for the examiners after the clinical examination.

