#### Implementation

The examiner who performs the first clinical examination will see and designate the allocation of each child using the opaque envelops. Then, she will inform it only to the examiners who will perform the visual inspection and treatment plans.

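### One fixed block size, with the first examiner seeing every allocation, could let some later assignments be deduced before inclusion and stratum are settled

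*Protocol article*

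**What the plan says.** Four statements in the protocol article matter together.

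- **Sequence generation:** "The randomization procedure will be done per blocks of the same size", with stratification by age and caries experience. The size is not given.
- **Strata (Interventions):** children are classified "according to age (3 and 4 years old or 5 and 6 years old) and according to the caries experience", with the dmf-s cut at 3. This makes four strata.
- **Concealment mechanism:** "We will use sealed, sequentially numbered, opaque envelopes, separated by each stratum".
- **Implementation:** "The examiner who performs the first clinical examination will see and designate the allocation of each child using the opaque envelops". She then passes the group on to the examiners who plan treatment.

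The content of the first examination is under Interventions: "An initial clinical examination will be performed to evaluate the teeth present in the mouth, as well as the caries experience". Having at least one primary molar is an inclusion criterion, and behavioural problems at the initial appointments are a ground for exclusion.

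The article also states safeguards. Children are drawn at random from the pool of enrollment forms. Randomisation follows inclusion and the radiographs. The planning examiners learn the group only after their own clinical examination.

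**The concern.** Sealed opaque envelopes hide the next assignment from someone who has no other information. Here one person sees every earlier assignment in each numbered series. With a constant block size, once one arm of a block is used up, the rest of that block is fixed. Anyone who has followed the series and knows the size can then name the next envelope without opening it.

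The same person's examination feeds two decisions that leave room for judgement. One is whether a child is excluded for behaviour. The other is whether a dmf-s score near 3 falls in the lower or the upper stratum, which decides the stack used. If the next assignment is known while these are open, inclusion or stratum could depend on the arm, consciously or not.

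What is at stake is selection bias in the primary comparison. Caries experience at baseline is plausibly prognostic for surfaces needing treatment, and the trial itself stratifies on it. The article also states its working hypothesis and says that it aims to refute the bitewing recommendation, so concealment should be above question.

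**Working it through.** **Inputs from the article.** Two parallel arms; equal numbers per group, from which 1:1 allocation is inferred; one block size, value not stated; four strata; 250 children planned and 225 included at submission. From Sample size: difference 5, SDs 15 and 10, two-sided 5%, 80% power, 103 per group.

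**Assumptions.** Block sizes of 2 to 10 are tried. The observer knows the size and has seen every earlier allocation in the stratum.

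**Step 1: the plan's own figure.** n per group = (15² + 10²) × (1.960 + 0.842)² / 5² = 325 × 7.849 / 25 = 102.04, rounded up to 103. This reproduces the stated number.

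**Step 2: share known with certainty.** An assignment is certain when all that remain in its block belong to one arm, so the certain ones form the final run of the block. In a balanced block of size b = 2m, the expected final run is 2m/(m + 1), and the share is 1/(m + 1). Check for b = 4: the orders AABB, ABAB, ABBA and their mirror images have final runs of 2, 1 and 1. The mean is 4/3, and 4/3 ÷ 4 = 33%.

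**Step 3: best-guess hit rate.** The observer guesses the arm with more places left. For b = 4 the four positions give 1/2, 2/3, 2/3 and 1; the mean is 2.833/4 = 71%. Other sizes were enumerated in the same way. Chance is 50%.

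| Block size | Certain | Best guess correct | Certain among 225 | Certain among remaining 25 |
|---|---|---|---|---|
| 2 | 50% | 75% | about 112 | about 12 |
| 4 | 33% | 71% | 75 | about 8 |
| 6 | 25% | 68% | about 56 | about 6 |
| 8 | 20% | 67% | 45 | 5 |
| 10 | 17% | 65% | about 38 | about 4 |

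The counts are upper limits. They assume complete blocks, a block size known from the start, and that all 225 have been randomised. They count determinable assignments, not biased ones.

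**Step 4: what the remedies achieve.** A simulation with randomly varied blocks of 4, 6 and 8 (assumed sizes, four strata of 62 children, 1,500 replicates, an optimal guesser who knows the set of sizes) gives about 2.4% certain, but still about 68% correct guesses. If the first examiner never learns past allocations, certainty is 0% and guessing is at 50%.

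**Step 5: power without the determinable assignments.** With blocks of 4, 206 × 2/3 = 137, about 69 per arm. The standard error is √(325/69) = 2.17, and 5/2.17 − 1.96 = 0.34, which gives power of about 63%. At 103 per arm the same formula gives 80%.

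**The case against.** The strongest reply is that the key premise is not in the article. It does not state the block size or say that the examiner knew it, and a condensed article may leave that to the full protocol. It also does not say who makes the final eligibility decision; that the first examiner does so is an inference from the content of her examination. This stands, and it makes the finding conditional.

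The safeguards also count. Software-generated random selection means that she cannot choose who comes next, and inclusion precedes the envelope. Moving a child between strata helps only someone who tracks the position of both stacks. All children have bitewings before randomisation, so sparing a child radiographs is no motive. Families, treating dentists and follow-up examiners are blinded. These points reduce the risk. They do not remove it: the timing of opening does not change what can be deduced from earlier envelopes, and random selection leaves the behavioural exclusion and borderline scoring open.

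A reader might go further and infer that the planning examiners' ICDAS examination is also predictable, because they are told each child's group. The documents do not support this. Prediction would also need each child's stratum and the envelope order, and nothing says that they receive either. The article says that they examine without knowledge of the group.

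**Conclusion.** The weakness is structural and worth correcting, but conditional. The article itself states the single block size, the separate series per stratum, and the examiner who sees every allocation and records the data for eligibility and stratum. If she knows or infers the block size, between 50% (blocks of 2) and 17% (blocks of 10) of assignments are determinable, and guesses on the whole sequence are right 65% to 75% of the time. This rests on 1:1 allocation, complete blocks and an assumed size.

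A reader might infer that allocation was steered or that the trial result is biased. Nothing in the article shows either, and no effect on the primary outcome can be estimated from it. With 225 of 250 children included, a change in procedure reaches few of them. The analysis is therefore where most of the protection can still be gained.

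**What to change.** **Children still to be randomised (about 25 at submission).** Separate allocation from enrolment and stratum assignment. Existing staff who do neither, for example the coordinator, open the envelope only after the ICDAS form is complete. The first examiner is not told the allocations. If only the planning examiner is available, she may open it at that point, but she would then handle the sequence herself, so this is second best. Randomly varied, undisclosed block sizes are a supplement: they remove most certainty but not better-than-chance guessing.

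**All children.** Report the block size, who knew it and who decided eligibility. Add a supportive sensitivity analysis of the primary outcome that leaves out assignments determinable from earlier ones in the block. Compare baseline dmf-s between arms within the determinable assignments, because that is where selection would show.

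**Cost.** A new list for the remaining envelopes, a change in who opens them, and one extra analysis; no added staff. Balance per stratum becomes slightly less exact if block sizes vary. The sensitivity analysis has lower power (about 63% with blocks of 4), so it should be judged on whether the estimate shifts, not on whether significance is kept.

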#### Outcomes

The primary outcome will be the number of dental surfaces with operative treatment needs in the follow-up. This outcome is composed of several mutually exclusive factors: number of surfaces with new dentin caries lesions; number of restored surfaces with necessity of replacement; tooth with pain episode and/or necessity of endodontic treatment and tooth indicated for extraction.

The separate components of the primary outcome will be considered as secondary outcomes. Other secondary outcomes will be the impact of oral health on quality of life, number of false-positive results, number of new lesions in the first permanent molars, cost-efficacy and quality-adjusted life year.

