#### Statistical methods

For comparing the outcomes between the two groups, Student’s *t* test and Poisson regression analysis will be performed. With regard to the impact of Oral Health on quality of life, differences in the final and baseline scores will be compared between the groups through Student’s *t* test or the Mann–Whitney test, depending on the normality of the data distribution.

Multivariate analysis will be conducted to investigate the influence of the radiographic examination on treatment decision. Time and treatment cost will be compared by Student’s *t* test. An incremental cost-efficacy ratio will be used to compare the economic impact of both diagnostic strategies, considering both the initial examination and possible treatment and re-treatments during the study. The quality-adjusted life year (QUALY) will be also calculated in order to estimate the ratio of cost saved/spent by the use of the proposed diagnostic strategy. For all analyses, the level of significance will be set at 5 %.

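### Randomisation is stratified by age group and caries experience, but no stated outcome comparison carries the strata and none is named primary; the cost is modest lost precision, not bias

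*Protocol article*

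**What the plan says.** All references are to the protocol article.

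- **Allocation: sequence generation.** Randomisation uses equal-sized blocks and is "stratified by age and caries experience groups". The section on the allocation concealment mechanism keeps a separate set of envelopes for each stratum.
- **Interventions.** The strata come from a first examination: "An initial clinical examination will be performed to evaluate the teeth present in the mouth, as well as the caries experience". Age is split as 3-4 or 5-6 years and caries experience as dmf-s at most 3 or above 3, which makes 2 x 2 = 4 strata.
- **Outcomes.** "The primary outcome will be the number of dental surfaces with operative treatment needs in the follow-up". It is a count of surfaces per child.
- **Statistical methods.** "For comparing the outcomes between the two groups", the section names two methods, Student's t "test and Poisson regression analysis will be performed". It attaches no stratification factor or covariate to either and does not say which is primary. The one analysis described as multivariate has another target: "Multivariate analysis will be conducted to investigate the influence of the radiographic examination on treatment decision".
- **Sample size.** The expected mean is 19 surfaces with visual inspection alone. The difference sought is 5 surfaces, the SDs are 15 and 10, the test is two-sided at 5% with 80% power, and the result is 103 per group.

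**The concern.** Stratified allocation forces the arms to be nearly equal on age group and dmf-s group. To the extent that these groups predict later treatment need, the true variance of the difference between arms falls. An analysis that leaves the strata out still counts the between-stratum variance as error. It therefore reports a standard error larger than the true one, rejects less often than its nominal 5%, and gives too wide an interval.

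Interval width matters in this trial. The abstract's working hypothesis is that radiographs add little and that visual inspection is sufficient. A conclusion of little or no difference depends on how tightly the interval excludes differences that matter, and the plan sets the important difference at 5 surfaces.

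**Working it through.** **Inputs from the article:** difference 5, SDs 15 and 10, two-sided alpha 0.05, power 0.80, 103 per group.

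**Input not in the article:** R2, the share of within-arm outcome variance explained by the four strata. I take 0.05 to 0.30 as an assumed range. The formulas are linear-model, normal approximations.

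**Step 1. Reproduce the plan's figure.**
n per arm = (15² + 10²)(1.960 + 0.842)² / 5² = 325 x 7.849 / 25 = 102.04, rounded up to 103. This is the printed number, with no allowance for stratification. Normal-approximation power at 103 is 80.4%; a noncentral t calculation gives 80.0%.

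**Step 2. Standard error without the strata.**
SE = sqrt(325/n), which is 1.776 at n = 103 and 1.803 at n = 100. The 95% half-width at n = 100 is 1.96 x 1.803 = 3.53 surfaces. The value n = 100 assumes that 20% of the 250 children are lost, since 250 x 0.80 / 2 = 100. The article prints an attrition rate of 80%, which does not lead to 250; that is a separate matter.

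**Step 3. Effect of the strata.** Let k = sqrt(1 - R2).

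- True SE under stratified allocation, also estimated by the adjusted analysis: k x SE.
- Adjusted power: Phi(5/(k x SE) - 1.96).
- Actual power of the unadjusted test: Phi((5/SE - 1.96)/k). The true spread is smaller, but the test still divides by the larger SE.
- Actual two-sided size of the unadjusted test: 2(1 - Phi(1.96/k)).
- Narrowing of the interval from adjustment: 1 - k.

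| R2 (assumed) | Actual size, unadjusted | Power at 103: unadjusted / adjusted | Power at 100: unadjusted / adjusted | Half-width at 100, adjusted | Narrowing |
|---|---|---|---|---|---|
| 0.05 | 4.4% | 81.0% / 82.3% | 79.8% / 81.2% | 3.44 | 2.5% |
| 0.10 | 3.9% | 81.6% / 84.3% | 80.4% / 83.2% | 3.35 | 5.1% |
| 0.20 | 2.8% | 83.0% / 88.2% | 81.8% / 87.3% | 3.16 | 10.6% |
| 0.30 | 1.9% | 84.7% / 92.0% | 83.5% / 91.2% | 2.96 | 16.3% |

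The gain from adjustment is 1.4, 2.7, 5.2 and 7.3 points at 103 per arm, and 1.4, 2.8, 5.5 and 7.8 points at 100 per arm.

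The unadjusted column must not be held at the planning value of 79% (n = 100) or 80% (n = 103). Stratified allocation raises the unadjusted test's own power slightly, so comparing adjusted power with the planning value would overstate the gain.

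**The case against.** The strongest reply is that the article does not commit to an unadjusted primary analysis. It names Poisson regression beside the t test. That model suits a count and can carry both stratification factors, and covariate lists are commonly left to an analysis plan, which is not shown here. A reader might infer that the t test is the sole primary analysis, or that baseline dmf-s and the teeth present go unused. The article supports neither: it designates no primary method, and dmf-s is already used to form the strata. A reader might also suppose that the strata were chosen because they predict caries, but no reason is given.

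This part of the reply stands, and it limits the point. A missing covariate list alone would not be worth raising. What remains is that one of the two named methods, Student's t test, cannot carry strata, that the sample size rests on the same unadjusted comparison, and that nothing says which method decides the trial.

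Two stronger readings also fail. Omitting the strata does not bias the estimate or inflate type I error; the error is on the conservative side. Nor does it leave the trial underpowered: at 103 per group the unadjusted test keeps at least its planned power at every R2 considered.

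One qualification concerns the Poisson model. The conservative direction assumes a standard error that reflects the real spread of the counts. The planning variances, 225 and 100, far exceed the means, 19 and 14 (14 if the difference of 5 is a reduction). Poisson errors taken from the model alone would be too small for that separate reason.

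**Conclusion.** The point holds as a mismatch between a stratified design and a stated analysis in which no comparison of the primary outcome is tied to the strata. The consequence is a conservative test and a wider interval than necessary. If the strata explain 5% to 30% of outcome variance, the loss is about 1 to 8 power points at 100 to 103 per arm, and adjustment narrows the interval by about 3% to 16%. If they explain almost nothing, the loss is close to zero. If the Poisson model is primary and already includes both factors, there is no loss.

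The size rests on the assumed R2, on a linear approximation to what may be a count model, and, for 100 per arm, on reading attrition as 20%. This is an inexpensive improvement worth making, not a threat to validity.

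**What to change.** Name one primary model for the number of surfaces needing operative treatment and include age group (3-4 or 5-6) and dmf-s group (at most 3 or above 3) as terms. A count regression with robust or overdispersion-corrected standard errors would suit the outcome. Continuous baseline dmf-s may be added as an option; it is a refinement, and the figures above do not include any gain from it. Report the adjusted comparison as primary, with its confidence interval, and the unadjusted comparison as a sensitivity analysis.

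The cost is a change of wording in the analysis section, made before allocation is linked to outcomes. Age and caries experience are already recorded at the first examination, so no new data, visits or children are needed, and 103 per group can stand.
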